#### Randomisation and data collection

Inclusion criteria and exclusion criteria are reported in detail in the study protocol [9]. Infants are eligible if diagnosed with an isolated left-sided CDH on prenatal ultrasound with gestational age at delivery ≥ 35.0 weeks [9]. Exclusion criteria are right-sided and bilateral CDH, antenatal diagnosed major associated structural or genetic abnormalities, high urgency caesarean section (intended interval to delivery < 15 min), cases that have been treated during pregnancy with experimental drug therapy aiming to decrease the occurrence of pulmonary hypertension, twin pregnancies in which the infant diagnosed with CDH is born first, multiple birth > 2, and placental abnormalities (i.e. anterior placenta praevia, placental abruption). Written informed consent from both parents is required for inclusion. Eligible fetuses will be randomised 1:1 to either PBCC or the standard approach of immediate cord clamping. Study procedures regarding PBCC and immediate cord clamping are explained in the study protocol [9]. Blinding of the allocation arm during intervention is not possible due to the nature of the intervention. Allocation will be stratified by predicted lung size (determined by observed to expected lung-to-head ratio and liver position, graded as mild/moderate/severe lung hypoplasia, measured between 20 and 26 weeks of gestation or at initial visit) and by treatment centre, using variable random permutated block sizes (4-8) [13]. Randomisation and data collection are performed in the electronic data capture system Castor EDC. This electronic database facilitates on-site data entry and ensures concealment of allocation. Security is guaranteed with login names, login codes, and two factor authentication. Only dedicated and trained co-investigators in each centre receive credentials for Castor EDC and are thus allowed to enter data and randomise patients. Patient data are collected until the end of the study period, which is defined as discharge from the tertiary care hospital or death before discharge depending on which occurs first and with a maximum study duration of 6 months.

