**Primary outcome**					
Pulmonary hypertension (defined as at least 2 out of 4 criteria for pulmonary hypertension *or* need for ECMO therapy in the first 24 h) after birth *in the total study population*	*n* (%)	*n* (%)	*p*	Difference (95% CI)	RR (95% CI)
Pulmonary hypertension or need for ECMO therapy in the first 24 h after birth* in subgroups with estimated:*					
*- Mild pulmonary hypoplasia*	*n* (%)	*n* (%)	*p*	Difference (95% CI)	RR (95% CI)
*- Moderate pulmonary hypoplasia*	*n* (%)	*n* (%)	*p*	Difference (95% CI)	RR (95% CI)
*- Severe pulmonary hypoplasia*	*n* (%)	*n* (%)	*p*	Difference (95% CI)	RR (95% CI)
**Secondary outcomes**^c^					
Mortality before discharge from tertiary care hospital	*n* (%)	*n* (%)		Difference (95% CI)	RR (95% CI)
Presence of ≥ 3 criteria for pulmonary hypertension or extracorporeal membrane oxygenation within 24 h after birth	*n* (%)	*n* (%)		Difference (95% CI)	RR (95% CI)
ECMO therapy	*n* (%)	*n* (%)		Difference (95% CI)	RR (95% CI)
Number of days needing supplemental oxygen	Mean ± SD and median [IQR]	Mean ± SD and median [IQR]		Difference (95% CI)	
Number of days on mechanical ventilation	Mean ± SD and median [IQR]	Mean ± SD and median [IQR]		Difference (95% CI)	
Number of days of admission to tertiary care hospital	Mean ± SD and median [IQR]	Mean ± SD and median [IQR]		Difference (95% I)	
Postpartum haemorrhage (estimated maternal blood loss > 1000 ml)	*n* (%)	*n* (%)		Difference (95% CI)	RR (95% CI)

*CI* Confidence interval, *ECMO* Extracorporeal membrane oxygenation, *ICC* Immediate cord clamping, *IQR* Interquartile range, *OR* Odds ratio, *PBCC* Physiological-based cord clamping, *RR* Relative risk, *SD* Standard deviation

^a^Differences will be calculated as the absolute difference in percentages for dichotomous data or as the difference in medians and means for continuous data

^b^Relative risks will only be calculated for dichotomous data

^c^Secondary outcomes will be reported in the total study population and in the subgroup with survivors, respectively

**Table 3 Tab3:** Exploratory outcomes

	**PBCC (*****n***** = 70)**	**ICC (*****n***** = 70)**

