### Statistical methods specified in the study protocol

#### Sample size calculation

As has been reported in the study protocol, the background incidence of pulmonary hypertension was previously reported at 69.7% in the first week after birth [9, 16]. Based on a suggested clinically relevant reduction in pulmonary hypertension incidence of one third, a total sample size of at least 140 infants was calculated with 80% power and a two-sided type I error of 5%.

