### Statistical analysis plan

#### Overall principle

Statistical significance is set at *p* < 0.05, using two-sided tests. For all relevant outcomes, a 95% confidence interval (CI) will be reported. Statistical analyses will be performed using the computing environment R (R Core Team (2020), Vienna, Austria).

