#### Primary outcome

The effect of PBCC on the primary outcome will be analysed as a complete case analysis in the intention-to-treat population. The main effect of PBCC on pulmonary hypertension will be analysed using the chi-square test. To explore the effect of PBCC on pulmonary hypertension per strata, subgroup analysis per strata (estimated mild/moderate/severe pulmonary hypoplasia) will be performed. An additional sensitivity analysis applying mixed effect models will be conducted to investigate the specific strata. The primary outcome will also be reported as absolute differences in percentages with 95% CI and relative risks with 95% CI to compare the intervention group with the control group (Table 2).

Analysis of the primary outcome will be based on complete cases and by protocol the independent variables in this multivariable analysis cannot be missing as these are required for randomisation. In the rare event that evaluation of the primary outcome has not been performed in the first 24 h, e.g. in the event of mortality before echocardiographic evaluation, the dependent outcome (i.e. pulmonary hypertension) will be missing. To evaluate the robustness of our findings and potential bias by such missing data, we will perform a sensitivity analysis. In this sensitivity analysis, missing values will be imputed by using the ‘worst case’ observed in cases in which the primary outcome was assessed.

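### Table 2 gives each severity subgroup of the primary outcome its own unadjusted p-value, but no treatment-by-severity test is stated

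*SAP article*

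**What the plan says.** Under Statistical analyses, Primary outcome, the SAP tests the main effect with one chi-square test and then adds: "To explore the effect of PBCC on pulmonary hypertension per strata, subgroup analysis per strata (estimated mild/moderate/severe pulmonary hypoplasia) will be performed". The next sentence reads: "An additional sensitivity analysis applying mixed effect models will be conducted to investigate the specific strata". The terms of that model are not given.

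In Table 2 the three severity rows sit in the Primary outcome block, directly below the row for the total study population. Each has a p-value, an absolute difference and a relative risk (RR), the last two with 95% confidence intervals. There is no row or column for an interaction or heterogeneity result.

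Under Overall principle, one rule covers all tests: "Statistical significance is set at *p* < 0.05, using two-sided tests". No exception or adjustment is made for subgroups. For the secondary outcomes, by contrast, the SAP drops p-values to limit multiplicity, and those cells in Table 2 are empty.

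**The concern.** A per-stratum analysis is done to learn whether the effect of PBCC depends on the severity of lung hypoplasia. A within-stratum p-value answers a different question: whether that stratum alone shows a difference from zero. Its result depends on the size of the stratum and its event rate as well as on the effect. Significance in one class and not in another is therefore not evidence that the effect differs between them.

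At stake is how the final table will be read. Three p-values in the primary block invite a statement that PBCC works in one severity class and not in the others. The plan's own reason for withholding p-values from mortality and ECMO applies at least as strongly to three small subgroup comparisons.

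**Working it through.** **Inputs from the SAP (Sample size calculation; Randomisation and data collection).** Control rate: "the background incidence of pulmonary hypertension was previously reported at 69.7% in the first week after birth". Effect: "Based on a suggested clinically relevant reduction in pulmonary hypertension incidence of one third", so 0.697 × 2/3 = 0.465, a difference of 0.232. Size: "a total sample size of at least 140 infants was calculated with 80% power and a two-sided type I error of 5" per cent. Allocation is 1:1, hence 70 per arm.

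**Reproducing the stated figure.** Pooled-variance formula without continuity correction, mean rate 0.581:

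n = [1.960 × √(2 × 0.581 × 0.419) + 0.842 × √(0.697 × 0.303 + 0.465 × 0.535)]² / 0.232² = 69.6, so 70 per arm and 140 in total, with power 80.2%. With a continuity correction the total would be 156, so the design matches the uncorrected test.

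**Inputs that are assumptions.** The SAP gives no stratum sizes and no stratum-specific rates. Several sets are used below to show a range.

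**Step 1: no effect in any stratum.** For three independent tests at 0.05, 1 − 0.95³ = 14.3%. With discrete counts and an uncorrected chi-square test, the chance of at least one p < 0.05 is about 11% to 15% over the sets below. In the last set it is 13.1% uncorrected and 4.8% with a continuity correction. The SAP does not say which form is used.

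**Step 2: power within one stratum for the planned effect.** At 69.7% against 46.5%, power is 23% with 14 per arm, 36% with 23.3 per arm and 50% with 35 per arm.

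**Step 3: the same RR of 2/3 in every stratum.** With stratum powers a, b and c, P(all three significant) = abc, P(none) = (1−a)(1−b)(1−c), and P(mixed) is the remainder. Uncorrected chi-square:

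| Per arm (mild/moderate/severe) | Control rates | Powers | All three | Mixed |
|---|---|---|---|---|
| 23/24/23 | 69.7% in each | 37/40/37% | 5% | 71% |
| 18/35/17 | 69.7% in each | 33/50/29% | 5% | 71% |
| 28/28/14 | 69.7% in each | 41/41/22% | 4% | 69% |
| 23/24/23 | 50/70/90% | 22/40/69% | 6% | 79% |
| 18/35/17 | 50/70/90% | 20/50/53% | 5% | 76% |
| 28/28/14 | 50/70/90% | 24/42/47% | 5% | 72% |
| 17/32/21 | 40/72/92% | 12.6/52.5/69.8% | 4.6% | 83% |

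Last row: 0.126 × 0.525 × 0.698 = 0.046; 0.874 × 0.475 × 0.302 = 0.125; mixed = 1 − 0.046 − 0.125 = 0.829.

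**Step 4: the scale of a heterogeneity test.** In the last row, RR 2/3 turns 40/72/92% into 26.7/48.0/61.3%.
- Risk differences are 13, 24 and 31 percentage points.
- Odds ratios are (0.267/0.733)/(0.40/0.60) = 0.55, (0.48/0.52)/(0.72/0.28) = 0.36 and (0.613/0.387)/(0.92/0.08) = 0.14.

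A constant RR is thus a varying odds ratio. In simulation at these sizes, a logistic treatment-by-severity test (2 df) rejects in about 22% of trials, against about 6.5% when there is no effect in any stratum. A log-RR heterogeneity test rejects in about 3% of the constant-RR trials.

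**Step 5: power of the replacement.** Take three equal strata of 23.3 per arm, the planned effect in one of them and none in the other two. On the risk-difference scale the variances are (0.211 + 0.249)/23.3 = 0.0197 in the stratum with the effect and 2 × 0.211/23.3 = 0.0181 in each of the others. The weighted mean difference is 0.073 and the non-centrality is 0.159²/0.0197 + 2 × 0.073²/0.0181 ≈ 1.9 on 2 df. Power is about 21%.

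**The case against.** The best defence is that the plan is already modest here. The subgroup sentence is worded as exploration. There are only three subgroups, fixed in advance and defined by a stratification factor. Every row carries estimates with intervals, and no success rule is attached to any of them. All of this stands and limits the weight of the point. It does not supply a test of whether the effect differs, and the Table 2 rows carry no exploratory label.

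A reader might infer three stronger things that the document does not support.

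- *That the trial's type I error is inflated.* It is not. The main effect rests on one overall chi-square test at 5%, and the 11% to 15% concerns the subgroup rows only.
- *That the mixed model has no treatment-by-severity term.* The SAP does not say so. The terms are unstated, and a fuller plan may contain one. What can be said is that no such term or test is stated, and that Table 2 has no place for its result.
- *That a discordant pattern would be pure noise, or that a claim for one class is intended.* Where control rates differ, a constant RR implies different risk differences, which the plan also reports, so some real variation on that scale is expected. No intention to claim benefit in one class is stated.

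A further objection, that any treatment-by-severity test has low power, is correct. It is a reason to rely on estimates and intervals, not a reason to run three separate tests.

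**Conclusion.** The point holds as a poor choice of stated method, confined to the subgroup family. Three unadjusted within-stratum p-values in the primary block do not answer the question the strata raise, and they depart from the plan's own treatment of the secondary outcomes. With no effect, the chance of at least one p < 0.05 is about 11% to 15% uncorrected, and about 5% with continuity correction in the one assumed set quoted for it. With a constant RR of 2/3, a mixed pattern appears in about 69% to 83% of trials and all three are significant in only about 4% to 6%. These ranges rest on assumed stratum sizes and control rates and on the uncorrected test. The qualitative conclusion is the same in every set tried. The primary inference is unaffected. The change should be made, but the main result does not depend on it.

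**What to change.** Delete the p-values from the mild, moderate and severe rows of Table 2. Keep n (%), RR and risk difference with 95% confidence intervals, and label the rows exploratory.

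Add one sentence to the Primary outcome analysis that pre-specifies a single heterogeneity test across the three severity strata. It should name the scale, and that scale should match a reported effect measure (for example log-RR or risk difference), not the odds-ratio scale of a logistic interaction. If the mixed model is kept, state its terms and link, so that a treatment-by-severity result from it is not read on a different scale from the table.

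Say in the same place that the test has low power (about 21% in the example above), so a non-significant result does not show that the effect is the same in all classes.

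The cost is one carefully worded sentence and one table edit, with no new data and no change in sample size. The small downside is the weak test. The change should be made before outcome data are seen by arm.

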#### Secondary outcomes

To limit multiplicity, formal statistical analyses will be carried out for only a limited number of pre-defined secondary outcomes that were regarded most relevant from a clinical perspective (Table 2). When mortality competes with outcomes, the risk for these outcomes can be underestimated. Therefore, these secondary outcomes will be reported in both the group of survivors and the total study population. For continuous variables, we will report absolute differences in means and medians with 95% CI. For dichotomous variables, we will report relative risks with 95% CI and absolute differences in percentages with 95% CI. The results will not be adjusted for multiplicity and *p*-values will not be calculated. Additionally, the distribution of the data for each of the pre-defined continuous secondary outcomes will be presented in histograms.

All possible effort will be made to complete the dataset and we expect that data on the predefined secondary outcomes will be present in nearly all infants. Hence, we will not use imputation to complete the dataset in case of missing values. The number of missing data in secondary outcomes will be reported.

#### Exploratory secondary outcomes

Descriptive statistics will be used to report all exploratory secondary outcomes—including context-specific safety outcomes—in the intervention group and control group, separately, and formal statistical testing will thus not be performed. Continuous data will be reported as mean ± SD or median [IQR] depending on distribution, and categorical data will be reported as counts and percentages.

### Trial reporting and status

The trial will be reported following the principles laid out in the CONSORT statement [17]. The trial was initiated in the Erasmus MC in May 2020. Eight additional centres started recruitment of patients between August 2020 and March 2024. We anticipate on including the final patient end-2024.

## Data Availability

Data sharing is not applicable to this article as no datasets were generated or analysed during the current study.
